### Sample Size Calculation

This study uses the MoCA score as the sole primary outcome measure, focusing specifically on the change from baseline to week 8. The primary comparison of interest is the difference in therapeutic efficacy between the combined intervention group and the routine care group.

Based on previous literature concerning nonpharmacological TCM interventions for cardiovascular and cognitive conditions, we hypothesize that the improvement in MoCA scores in the combined intervention group after 8 weeks will exceed that of the routine care group by a clinically meaningful difference (△µ) of approximately 3 points. We acknowledge that the estimated effect size (standardized mean difference ≈0.7-0.9) cited in similar studies may appear optimistic. However, this anticipated 3-point improvement is supported by the moderate-to-strong effect trend consistently reported in meta-analyses of comparable TCM external therapies, justifying its use for the primary calculation.

Assuming an SD (σ) of approximately 4, a one-way ANOVA was used to estimate the required effective sample size. The significance level (α) was set at .05, and statistical power (1–β) at 0.80. The initial calculation indicated a required effective sample size of 33 participants per group.

Considering a potential dropout rate of 15%, the required number of participants to be recruited per group is calculated as approximately 33/(1‐0.15)=38.82. The final sample size was therefore rounded up to 39 participants per group to ensure adequate retention and statistical power, resulting in a total sample size of 156 participants.

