### Study Design

This study is designed as a prospective, single-center, randomized, single-blind, 4-armed parallel controlled clinical trial. A total of 160 eligible patients will be randomly assigned in a 1:1:1:1 ratio to one of four groups via a centralized randomization system: routine care group, Du-moxibustion group, spine-pinching group, and combined intervention group (Du-moxibustion+spine-pinching). The intervention will last for 8 weeks. The routine care group will receive health education once per week, while the other 3 groups will receive treatment twice per week: Du-moxibustion (30 min/session), spine-pinching (15‐20 min/session), and combined therapy (45‐50 min/session). Outcomes will be assessed at baseline, midintervention, postintervention, and follow-up.

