#### Primary Outcome Analysis

Analysis of the sole primary outcome is focused on the difference in MoCA scores at week 8 between the combined intervention group and the routine care group. We will use ANCOVA for this comparison, adjusting for the baseline MoCA score as a covariate, to derive the primary efficacy conclusion (significance level set at *P*<.05).

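### The 33 per group is credited to a one-way ANOVA, but the primary test is a two-arm ANCOVA that needs 28 or 29 per arm on the stated inputs; separately, the randomised total is given as both 156 and 160

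*Protocol article*

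**What the plan says.** All references are to the protocol article.

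- **Sample Size Calculation** names MoCA change from baseline to week 8 as the only primary outcome and combined intervention versus routine care as the primary comparison. The assumed difference is "of approximately 3 points" and the SD about 4. Alpha "was set at .05, and statistical power" was set at 0.80. The same section mentions a standardized mean difference of about 0.7 to 0.9 from similar studies.
- It then says that "a one-way ANOVA was used to estimate the required effective sample size", and continues: "The initial calculation indicated a required effective sample size of 33 participants per group". A 15% dropout allowance raises this to 39 per group, "resulting in a total sample size of 156 participants". The Abstract also gives 156.
- **Study Design** gives another total: "A total of 160 eligible patients will be randomly assigned", in a 1:1:1:1 ratio.
- **Primary Outcome Analysis** compares combined intervention with routine care at week 8: "We will use ANCOVA for this comparison, adjusting for the baseline MoCA score as a covariate".
- **Secondary and Exploratory Analysis** is where one-way ANOVA appears as an analysis method. **Strategy for Controlling Multiple Comparison Risk** confines inference and power evaluation to the primary comparison.

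**The concern.** A sample size statement should let a reader recompute the number of patients from the stated inputs, for the test that will decide the trial. Here the method named for sizing is not the method of the primary analysis. The inputs given, one pairwise difference and one SD, suit a two-arm calculation but are not enough for a four-group ANOVA. The two-arm calculation they do support gives a number other than 33.

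Two things are at stake. The 80% is not the power of the planned primary test, and it could be taken as a power claim for the four-group comparisons, for which the document gives no basis. The document also holds two different randomisation targets, which should be settled before recruitment, scheduled to start in March 2026.

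**Working it through.** **Inputs.** From Sample Size Calculation: difference 3, SD 4, alpha .05, power 0.80, dropout 15%. From Study Design and the randomisation section: equal allocation to four arms. Assumption: a two-sided test, as sidedness is not stated.

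**1. The dropout step reproduces.** 33/(1 − 0.15) = 38.82, rounded up to 39; 4 × 39 = 156. The other total implies 160/4 = 40 per arm, and 40 × 0.85 = 34 evaluable, a figure that appears nowhere.

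**2. The 33 as a two-arm comparison.** The implied standardized difference is d = 3/4 = 0.75.

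- Normal approximation: n = 2 × (1.960 + 0.842)² / 0.75² = 15.70/0.5625 = 27.9, so 28 per arm.
- Exact noncentral t: 29 per arm (power 80.1%). A two-group one-way ANOVA is the same test and also gives 29.
- Power at 33 per arm: normal, Φ(0.75 × √(33/2) − 1.960) = Φ(1.09) = 86.1%; exact t, 85.1%.
- Power at 39 per arm: 90.5% (exact t).

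Variants do not give 33 either. One-sided testing gives 22. Power of 90% gives 38 (normal) or 39 (t). A Bonferroni split over two comparisons, which the plan does not state for the primary test, gives 34 or 36. Baseline adjustment lowers the requirement: at an assumed baseline correlation of 0.5 (not in the document), 28 × (1 − 0.5²) = 21.

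**3. What does give 33.** With d = 0.70, n = 15.70/0.49 = 32.04, so 33 per arm by the normal approximation (34 by the t-test). That is the low end of the quoted 0.7 to 0.9 range, and it equals a 2.8-point difference with SD 4.

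**4. The 33 as a four-group ANOVA.** Power depends on all four means through f = √(Σ(mᵢ − m̄)²/4)/4, where the final 4 is the SD. Only the two extreme arms are specified, 3 points apart. Letting the single-therapy arms vary within that range:

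| Assumed means (routine / single / single / combined) | f | n per group for 80% | Power at 33 |
|---|---|---|---|
| 0 / 1.5 / 1.5 / 3 | 0.265 | 40 | 71% |
| 0 / 1 / 2 / 3 | 0.280 | 36 | 76% |
| 0 / 0.5 / 0.5 / 3 | 0.293 | 33 | 80% |
| 0 / 0 / 0 / 3 | 0.325 | 27 | 88% |
| 0 / 0 / 3 / 3 | 0.375 | 21 | 96% |

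The first and last rows are the least and most favourable patterns for a range of 3. So 33 lies inside the feasible span of 21 to 40 but can be neither confirmed nor refuted.

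**5. The totals.** 156 appears in the Abstract and is derived in Sample Size Calculation. 160 appears once, in Study Design, without derivation.

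**The case against.** The strongest defence has four parts.

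- **The inputs are approximate.** The document says about 3 and about 4, and never states 0.75. A sizing at 0.70 fits the range it mentions. This stands as an explanation of where 33 may come from. It does not show which effect size was used: the section adopts the 3-point difference for its primary calculation, and with SD 4 that is 0.75.
- **Under the method named, 33 is not shown to be wrong.** This stands in full. A reader might infer that the ANOVA figure is an error, or that the trial has only 71% power and needs 40 per group. The documents do not support that: those figures belong to the least favourable of many possible patterns, and one pattern gives exactly 33. An article may also leave the four means to a fuller protocol. What remains is that a four-group ANOVA is not the primary test, whatever means were assumed.
- **The discrepancy is harmless for the primary conclusion.** This also stands. The primary comparison has more power than claimed, and the four-group comparisons are declared exploratory.
- **156 is plainly the intended total.** It is derived and repeated, while 160 differs by one participant per arm. It would go too far to say that a reader has no idea of the target. Still, Study Design says all 160 are randomised, and nothing explains the difference. The four pilot participants would account for it numerically (156 + 4), as would a t-test sizing at 0.70 (34/0.85 = 40, and 4 × 40 = 160). Both are conjecture.

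**Conclusion.** The point holds as a mismatch and a contradiction, not as a shortfall in power.

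- The sizing method does not match the primary analysis. For a difference of 3, SD 4 and two-sided .05, the two-arm comparison needs 28 or 29 per arm for 80% power. The planned 33 evaluable per arm give about 85%, and 39 about 90%, with any gain from baseline adjustment on top. The stated 80% is conservative.
- A reader might infer that the trial is underpowered. On its own assumptions for the primary comparison it is not. No such statement, in either direction, can be made for the four-group test: power at 33 runs from 71% to 96% across the unstated means.
- The totals 156 and 160 contradict each other by 4 participants, or 1 per arm. The stated derivation supports only 156.

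The figures rest on a two-sided test and on taking the approximate 3 and 4 at face value.

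**What to change.** 1. In Sample Size Calculation, replace the ANOVA sentence with a two-arm calculation (t-test or ANCOVA) for combined intervention versus routine care, stating sidedness and the effect size used.
2. Restate the power as about 85% at 33 evaluable per arm for a 3-point difference with SD 4. Alternatively, keep 80% and say that 33 is sized for a standardized difference of 0.70.
3. Say that no power is claimed for the four-group comparisons.
4. Reconcile the 160 in Study Design with the 156 in the Abstract and Sample Size Calculation; the derivation supports 156. State whether the four pilot participants are outside the randomised sample.

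The cost is wording only. No extra patients are needed, because 39 randomised per arm with 15% loss still leaves 33 evaluable (39 × 0.85 = 33.15), more than the primary comparison requires on the stated assumptions.

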#### Blinding

This study uses a single-blind design. Outcome assessors and data analysts will be blinded to group allocation, whereas intervention practitioners cannot be blinded due to the nature of Du-moxibustion and spine-pinching procedures. Participants will be informed they are receiving treatment but will not be told the specific group or intervention type (eg, Du-moxibustion or spine-pinching) to minimize expectation bias. All assessors will undergo standardized training in MoCA and Fried phenotype scoring to ensure objective and consistent evaluations. Statistical analysis will be performed by an independent third party, and raw data will be anonymized. In the case of emergencies (eg, serious adverse events), unblinding may occur, with reasons, timing, and actions recorded in the case report form (CRF). Final unblinding will occur after study completion and data analysis.

### Intervention Methods

All participants will receive standardized routine care as a basic treatment. Interventions will be administered by licensed TCM practitioners or trained technicians according to standardized procedures to ensure consistency. During the intervention period, participants will be instructed to avoid receiving any additional external TCM treatments or other therapies that may affect CF.

### Routine Care Group

Participants in the control group will receive 30-minute health education sessions twice per week, conducted by registered nurses in classrooms or consultation rooms. Education will be delivered using Microsoft PowerPoint presentations, video demonstrations, and interactive Q&A sessions. Printed health education manuals will also be provided. The curriculum includes:

Dietary guidance: low-salt, low-fat diet with balanced nutrition (eg, omega-3-rich fish, fruits, and vegetables);Exercise advice: moderate aerobic exercise (eg, 30 min of brisk walking or Tai Chi daily);Cognitive health strategies: memory training techniques (eg, associative memory and number games) and psychological health management.Frequency and duration: twice per week for 8 consecutive weeks (total of 16 sessions).Safety: any psychological or emotional discomfort (eg, anxiety) reported after sessions will be recorded. No invasive procedures are involved.

### Du-Moxibustion Group

Details pertaining to the participants in the Du-moxibustion group are as follows:

Treatment site: this implies the Du meridian line, from Dazhui (GV14) to Yaoshu (GV2), covering thoracic vertebrae T1 to lumbar vertebrae L5, as illustrated in Figure 1.Materials: these include a herbal powder (equal parts of astragalus, codonopsis, chuanxiong, and carthamus), fresh ginger paste (thickness: 1.5 cm), mulberry paper, moxa cones (1.5 cm diameter, approximately 2 g each), alcohol swabs, and an ignition device.Procedure: these include (1) the participant lying in the prone position; (2) the back is cleaned and dried; (3) the herbal powder is applied along the Du meridian, covered with mulberry paper; (4) a 1.5 centimeter layer of ginger paste is spread over the area; (5) Moxa cones are placed in shallow depressions formed in the ginger layer; (6) the cones are ignited and burned for approximately 30 minutes, and (7) the residues are cleaned and the skin is inspected for irritation or burns.Environment: the treatment room must be well-ventilated and equipped with smoke evacuation systems.Frequency and duration: the frequency is twice per week for 8 consecutive weeks (total of 16 sessions). The session duration of Du-moxibustion was set at 30 minutes based on previous clinical trials, in which moxibustion treatments typically lasted 20 to 30 minutes, ensuring both sufficient stimulation and patient safety [16].Safety monitoring: skin reactions (eg, redness and burns) will be observed after each session. Cold compresses or suspension of treatment will be applied if necessary. All findings will be recorded in the CRF.

**Figure 1. F1:**
[figure not shown]
Acupoints and treatment area for Du-moxibustion along the Du meridian (GV14–GV2).

### Spine-Pinching Group

Details pertaining to the participants in the spine-pinching group are as follows:

Position: the position should be prone, with the back exposed.Method: starting from the sacrococcygeal region along the midline of the spine, pinch the skin and move upward toward the seventh cervical vertebra. The procedure is performed along 3 lines centered on the spine (left bladder meridian, right bladder meridian, and Du meridian). For each line, perform 3 pinches, followed by lifting (pinch 3 times and lift once) for 4 to 5 cycles. Acupressure is applied to the Xinshu (HT7), Shenshu (KI3), Pishu (SP3), Weishu (ST25), Ganshu (LV3), and Sanjiaoshu (SJ5) points (1 min per acupoint). The acupoint locations are shown in Figure 2, and the manipulation technique is illustrated in Figure 3. The total treatment duration is 15 to 20 minutes.Frequency and duration: the frequency is twice per week for 8 weeks, totaling 16 sessions.Safety: after each intervention, skin tenderness or muscle discomfort will be monitored and recorded in the CRF.

**Figure 2. F2:**
[figure not shown]
Acupoint locations used in spine-pinching therapy.

**Figure 3. F3:**
[figure not shown]
Manipulation technique of spine-pinching therapy.

### Combined Intervention Group

Details pertaining to the participants in the combined intervention group are as follows:

Intervention order: following the “first unblock, then replenish” principle, spine-pinching therapy is performed first (to unblock meridians and regulate qi and blood), followed by Du-moxibustion (to warm and regulate the Du meridian and tonify the kidney and marrow).Procedure: the spine-pinching procedure is the same as described in the “Spine-Pinching Group” section, and the Du-moxibustion procedure is the same as described in the “Du-Moxibustion Group” section. The total treatment time is 45 to 50 minutes.Environment: the treatment room should have proper ventilation and be equipped with smoke-extraction devices.Frequency and duration: the frequency is twice per week for 8 weeks, totaling 16 sessions.Safety: after each intervention, skin redness, burns, or tenderness will be monitored. If necessary, cold compresses or suspension of treatment will be applied, and the results will be recorded in the CRF.

### Intervention Adherence Management

A dedicated team member will record the execution of interventions and patient feedback. Prior to each session, the research nurse will inform, supervise, and reassure the participants. If a participant misses 2 consecutive sessions or completes less than 80% of the interventions, the reasons will be analyzed, and a decision will be made regarding their inclusion in the final analysis.

#### Primary Outcome Measures: Cognitive Function

Cognitive function will be assessed using the Chinese version of the MoCA. The total score ranges from 0 to 30, with higher scores indicating better cognitive function. The primary outcome is the change in MoCA scores from baseline. Evaluations will take place at weeks 0, 6, 8, and 12.

#### Secondary Outcome Measures

##### Physical Frailty

Physical frailty will be assessed using the Fried Frailty Phenotype Scale (0‐5 points). A score of 1 to 2 indicates prefrailty, and ≥3 indicates frailty. The scale includes measures of weight loss, fatigue, grip strength (measured using a standard dynamometer), walking speed (measured by a 4-m walking test), and physical activity reduction. Evaluations will be conducted by assessors at weeks 0, 6, 8, and 12. The main focus will be to observe whether participants transition from “prefrailty” to “nonfrailty.”

##### Activities of Daily Living

Activities of daily living will be assessed using the Barthel Index (0‐100 points, with higher scores indicating better function). The index includes 10 items related to basic daily activities such as feeding, bathing, and dressing. Assessments will be made at weeks 0, 6, 8, and 12.

##### Quality of Life

Quality of life will be measured using the Short Form Health Survey, self-administered by participants. It includes 8 dimensions, with scores ranging from 0 to 100. The results are summarized into 2 components: physical health component summary and mental health component summary, with higher scores indicating better quality of life. Evaluations will occur at weeks 0, 6, 8, and 12.

##### Depression Status

Depression will be assessed using the 15-item Geriatric Depression Scale, with a total score ranging from 0 to 15. A score ≥5 suggests the presence of depressive symptoms, and higher scores indicate greater depression severity. The scale will be administered through an interview conducted by an assessor. Evaluations will occur at weeks 0, 6, 8, and 12.

##### TCM Syndrome Score

The TCM syndrome score will be based on the syndrome differentiation criteria for “spleen-kidney deficiency with Du meridian obstruction.” The scale includes items such as dizziness, memory loss, physical weakness, insomnia, and soreness in the waist and knees. A 4-point Likert scale will be used, with higher scores indicating more severe symptoms. Evaluations will be conducted at weeks 0, 6, 8, and 12.

##### Evaluation Time Points

All outcome measures will be assessed at the following time points: baseline (week 0), midintervention (week 6), postintervention (week 8), and follow-up (week 12).

##### Data Management

CRFs will be completed on paper by data entry officers, and the data will be independently entered into a password-protected Microsoft Excel database by 2 trained personnel. Any discrepancies will be cross-checked to ensure accuracy. All trial documents—including informed consent forms, CRFs, and intervention records—will be securely stored in encrypted electronic databases and locked cabinets, under the supervision of the study coordinator. Adherence to the intervention (eg, attendance rate and missed sessions) will be documented in the CRFs and collected at weeks 0, 6, 8, and 12. Participant confidentiality will be maintained during result dissemination. At least one audit by the hospital’s ethics committee or research oversight body will be conducted to assess data completeness and regulatory compliance.

### Statistical Analysis

#### Overview

Data analysis will be conducted using SPSS (version 27.0; IBM Corp). The primary analysis will be based on the intention-to-treat principle, supplemented by per-protocol analysis. Missing data will be imputed using the last observation carried forward method. Results will be expressed as mean (SD) or median (IQR), as appropriate.

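### Last observation carried forward is the only missing-data method for the week-8 MoCA comparison, and it freezes dropouts at an earlier score, which biases the estimated difference

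*Protocol article*

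**What the plan says.** All references are to the protocol article.

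- Statistical Analysis, Overview, sets the population: "The primary analysis will be based on the intention-to-treat principle, supplemented by per-protocol analysis". It then gives the only rule for missing values: "Missing data will be imputed using the last observation carried forward method". No other method and no missing-data sensitivity analysis is named. The per-protocol analysis changes the population; it does not handle missing scores.
- Primary Outcome Analysis defines the target as "the difference in MoCA scores at week 8 between the combined intervention group and the routine care group" and the model: "We will use ANCOVA for this comparison, adjusting for the baseline MoCA score as a covariate".
- Evaluation Time Points places MoCA at weeks 0, 6, 8 and 12.
- Sample Size Calculation plans for loss ("Considering a potential dropout rate of 15" percent) and expects the combined arm to gain more than routine care by a "clinically meaningful difference (△µ) of approximately 3 points".
- Criteria for Withdrawal or Discontinuation lets people who withdraw or are lost be left out of the analysis. Intervention Adherence Management leaves the inclusion of poor attenders to a later decision.

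**The concern.** LOCF is a stated rule for the trial's single confirmatory test, so it is not a detail left to an unseen analysis plan. For a missing week-8 score there are only two earlier values to carry. Loss before week 6 carries baseline, which is a change of zero. Loss between weeks 6 and 8 carries the week-6 value. Both assume that nothing happens after the last visit, while the sample size rests on a relative gain of about 3 points by week 8. Change under routine care is plausible too, because the health education includes memory training.

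The estimated week-8 difference is at stake. If the combined treatment works and dropout is similar in both arms, the estimate is pulled towards zero. If dropout differs by arm and the arms share a common change, a difference can appear where none exists.

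**Working it through.** **The plan's own figure.** 33/(1 − 0.15) = 38.8, rounded up to 39 per arm, and 4 × 39 = 156. This step reproduces. Expected loss is 0.15 × 39 = 5.85, about 6 per arm. The starting figure of 33 is taken as given. A plain two-sample calculation with difference 3 and SD 4 needs 28 to 29, so 33 is not short for this contrast.

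**Inputs from the protocol.** Difference 3, SD 4, 15% dropout, 39 per arm, visits at weeks 0, 6 and 8, ANCOVA on baseline.

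**Inputs assumed.** Correlation 0.6 between baseline and later scores and 0.8 between weeks 6 and 8; 75% of the change reached by week 6; dropout at random; two-sided 5% test. Timing of dropout and its split by arm are varied.

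**Formula.** In an arm with dropout d, share p of dropouts lost before week 6, and mean changes m6 and m8, the expected LOCF change at week 8 is

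(1 − d) × m8 + d × (1 − p) × m6.

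**True difference 3, 15% dropout in both arms** (combined m8 = 3, m6 = 2.25; routine care 0):

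- All lost before week 6: 0.85 × 3 = 2.55.
- Half before week 6: 2.55 + 0.15 × 0.5 × 2.25 = 2.72.
- All have a week-6 score: 2.55 + 0.15 × 2.25 = 2.89.

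Simulation of the planned ANCOVA (6,000 replicates) agrees:

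| Dropout timing | LOCF estimate | Model SE | Actual SD of estimates | 95% coverage |
|---|---|---|---|---|
| All before week 6 | 2.55 | 0.703 | 0.689 | 90.7% |
| Half before week 6 | 2.71 | 0.717 | 0.718 | 93.2% |
| All after week 6 | 2.90 | 0.728 | 0.724 | 95.0% |

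ANCOVA on observed week-8 scores under the same random dropout gives 2.99 to 3.01, SE about 0.79 and coverage of about 95%.

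**True difference 3, dropout 10% routine care and 20% combined, half early** (gains of 1 and 4 points by week 8):

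- Combined: 0.8 × 4 + 0.2 × 0.5 × 3 = 3.50.
- Routine care: 0.9 × 1 + 0.1 × 0.5 × 0.75 = 0.94.
- Difference: 2.56 (simulated 2.55).

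**No true difference, both arms gain 2 points** (1.5 by week 6). Each dropout loses 2 − (1 − p) × 1.5 points: 1.25 if half are early, 2 if all are. The shift, combined minus routine care, is that loss times (routine dropout − combined dropout):

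| Routine / combined dropout | Half early | All early | Simulated type I error |
|---|---|---|---|
| 15% / 15% | 0 | 0 | – |
| 20% / 10% | 0.10 × 1.25 = +0.13 | – | about 5.5% (half early) |
| 25% / 5% | 0.20 × 1.25 = +0.25 (simulated +0.27) | 0.20 × 2 = +0.40 | 6.6% to 8.3% |
| 5% / 25% | −0.25 (simulated −0.26) | −0.40 | – |

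**The case against.** Four objections carry weight.

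**The harm at the planned dropout is modest.** With 15% in both arms the bias is towards zero, and power barely moves: with half of dropouts early, the simulated rejection rate is 96.5% under LOCF and 96.1% on observed scores. This stands. It limits severity but does not make the estimate right.

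**The standard error is not wrong.** A reader might infer that LOCF gives falsely narrow error bars because filled values count as observed. The calculations do not support that here: the model SE matches the actual spread of the LOCF estimates. Coverage falls because the interval is centred on a biased value.

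**Burns and long sessions do not manufacture a benefit when both arms improve.** A reader might infer that extra dropout in the combined arm would create a false positive. With a shared gain, the shift then goes against the combined arm (about −0.26). The spurious benefit needs heavier loss from routine care, and the 25%/5% split is an assumption; the protocol gives only 15% overall. At 20%/10% the shift is 0.13.

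**The benchmark is favourable.** Likelihood-based estimates returned 3.00 to 3.01, but under random dropout, where observed-case ANCOVA also does well. Dropout that depends on unseen scores was not tested. This stands, and is a reason to keep sensitivity analyses.

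A further limit is that, if the withdrawal and adherence rules were used to remove dropouts, LOCF would hardly operate and these figures would not apply. That would not rescue the plan, because intention-to-treat would then be abandoned.

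**Conclusion.** The point holds as a moderate one that should be corrected. The stated rule biases the week-8 difference whenever MoCA changes after the last carried visit and that change or the dropout differs between arms. For a true difference of 3 and 15% dropout in both arms, the estimate is about 2.55 to 2.72 with 91% to 93% coverage, or 2.89 if every dropout has a week-6 score. Unequal dropout can bias the null comparison in either direction, by 0.13 to 0.40 points in the cases worked. With equal dropout and no effect there is no bias.

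The mechanism follows from the protocol's visit schedule and its own hypothesis. The sizes rest on assumed timing, split by arm, trajectories and correlations. The documents do not support a claim that LOCF would overturn the trial's conclusion at the planned dropout.

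**What to change.** Replace LOCF in the primary analysis with one of two methods:

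1. Multiple imputation by arm, using MoCA at all visits, followed by the planned ANCOVA at week 8.
2. A likelihood-based repeated-measures model on MoCA at weeks 0, 6, 8 and 12, with baseline as a response constrained equal across arms, reading combined minus routine care at week 8.

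Baseline should be a response in the second option. If it is only a covariate, participants lost before week 6 have no post-baseline response unless they return, and contribute nothing, which sits badly with intention-to-treat.

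Keep LOCF as a sensitivity analysis only. In the same edit, reconcile Criteria for Withdrawal or Discontinuation and Intervention Adherence Management with the intention-to-treat statement, so that it is clear who is in the primary analysis.

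The cost is wording and slightly more model specification. No new data are needed and the sample size stays at 39 per arm. Expect a somewhat larger standard error: observed-score ANCOVA gave about 0.79 against 0.70 to 0.73 for LOCF at 15% dropout. The exact figure for the two recommended methods was not calculated.
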